### Data collection

Study data will be collected and managed using REDCap™ electronic data capture tools hosted at the Lausanne University Hospital. Collection of both quantitative and qualitative data for the objective 1 will comprise (a) online questionnaires completed by the teaching nurses at pre- and post-implementation phases to assess changes in barriers to implementation and beliefs and attitudes regarding the importance of patient activation; (b) online questionnaires at pre-implementation phase for nurse managers to assess units’ readiness for research utilization in practice and structural and organizational environment; (c) a TDF-based focus group with teaching nurses at pre-implementation phase to qualitatively assess perceived barriers to discharge teaching; (d) online questionnaires at post-implementation phase for teaching nurses to assess feasibility, acceptability and appropriateness of the intervention; (e) self-reported measure by teaching nurses of intervention fidelity during implementation phase; and (f) a focus group with teaching nurses at post-implementation phase to assess the appropriateness and the relevancy of the implementation strategies (Fig. 3).

**Fig. 3 Fig3:**
[figure not shown]
Data collection and implementation process

Collection of quantitative data for the objective 2 will comprise (a) patient participants questionnaires at the beginning of the hospital stay, the day of discharge and a telephone survey 7–10 days after discharge and (b) chart reviews to collect participants’ socio-demographic and medical data, and readmissions within 7 days (Figs. 2 and 3).

### Study measures

#### Objective 1: Test the feasibility of implementing the nursing discharge teaching intervention

*Changes in behavioural determinants* regarding the implementation of the intervention will be assessed with the Determinants of Implementation Behavior Questionnaire (DIBQ), which is based on the TDF domains [51]. The DIBQ will be completed by teaching nurses at pre- and post-implementation phase. The questionnaire comprises 93 items, investigating 18 domains of behavioural determinants: knowledge, skills, social/professional and role and identity, beliefs about capabilities, optimism, beliefs about consequences, intentions, goals, innovation, socio-political context, organization, patient, innovation strategy, social influences, positive emotions, negative emotions, behavioural regulation and nature of the behaviours. Responses are scored from 1 (strongly disagree) to 7 (strongly agree). Discriminant content validity with the TDF domains resulted in items discriminately assessing 11 out of the 14 domains [52]. Internal consistency values of the 18 domains range from 0.68 to 0.93 [51]. The DIBQ will be translated into French according to Wild’s method [53].

*Changes in nurses’ attitudes* regarding the importance of patient self-management behaviours will be evaluated with the Clinician Support for Patient Activation Measure (CS-PAM) [54]. The CS-PAM will be completed by teaching nurses at pre- and post-implementation phases. The CS-PAM consists of 14 items taken from the PAM and prefaced with the question “As a clinician, how important is it to you that patients…”. Responses are scored on a 4-point Likert scale from *Extremely important* to *Not important*. Data of CS-PAM will be sent to Insignia Health®, the licensing rights supplier for this instrument, who will score the data and send the results back [50]. This 14-item measure had a Cronbach’s alpha of 0.86, and Rasch analysis provided an overall person reliability of 0.80 tested with primary care clinician [54]. As no French-version is available, the CS-PAM will be translated according to Wild’s method [53].

*Acceptability, appropriateness and feasibility* of the intervention will be evaluated in the post-implementation phase by teaching nurses with three implementation outcome measures recently developed by Weiner et al. [55] to assess the success of implementation efforts: Acceptability of Intervention Measure (AIM), Intervention Appropriateness Measure (IAM) and Feasibility of Intervention Measure (FIM). Each measure has 4 items, with scale values ranging from 1 (completely disagree) to 5 (completely agree). Higher scores indicate greater acceptability, appropriateness and feasibility. These three measures have demonstrated promising psychometric properties: Cronbach alphas of 0.85 for AIM, 0.91 for IAM and 0.89 for FIM and test-retest reliability of 0.83 (AIM), 0.87 (IAM) and 0.88 (FIM) [55].

*Fidelity* of the discharge teaching delivery will be determined by entry of intervention activities on the Discharge Teaching Guide. Nurses will use a Discharge Teaching Guide for each patient enrolled in the study, on which they will record in check boxes each intervention they delivered to their patient. A descriptive interpretation will be done to analyse the level of fidelity.

*Appropriateness* of implementation strategies will also be explored through a focus group conducted by the researcher with teaching nurses during the post-implementation phase. The nurses will be asked which implementation strategies were most useful to them in facilitating the implementation and the delivery of the discharge teaching intervention.

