##### Patient activation

Participants will be asked by teaching nurses to complete the Patient Activation Measure (PAM). The PAM is a 13-item self-report questionnaire to measure patient activation level [43]. Patients can go through four levels of activation: (1) disengaged and overwhelmed, (2) becoming aware but still struggling, (3) taking action and (4) maintaining behaviours and pushing further. Stages of activation are distributed as follows in the PAM items: items 1–2, believing an active role is important; items 3–8, having confidence and knowledge to take action; items 9–11, taking action; and items 12–13, continuing healthy behaviours under stress. Responses range from 1 = “strongly disagree” to 4 = “strongly agree”. PAM raw score can be calculated by adding all of the responses to the 13 questions. This score is then converted into an activation score ranging from 0 = no activation to 100 = high activation using a scoresheet provided by Insignia Health®. Psychometric properties of the PAM in hospitalized multimorbid patients showed a satisfying reliability (Cronbach’s alpha = 0.88) and a content validity index of 0.91 [48]. Another study in the inpatient setting provided evidence for the internal consistency reliability (Cronbach’s alpha = 0.81) and the construct validity of the PAM-13 [49]. A PAM research license will be obtained from Insignia Health®, which will provide a validated French version of the PAM-13 and the scoresheet [50]. The level of activation calculated with the PAM will define which category of Discharge Teaching Guide the nurses will use. The guide corresponding to the participant activation level will guide them towards which objectives related to self-management domains are realistic based on this level. Levels 1 and 2 describe patients who are rather passive recipients of care and who lack basic health knowledge, for whom the objectives aim at increasing the awareness or basic knowledge of their health information. Teaching objectives for patients with a moderate level of activation (level 3) aim to support them in developing their knowledge and skills in managing their health and encourage them to play a more active role in their care. For patients with a high level of activation (level 4), the objectives aim to complete missing knowledge and help them to prevent relapses.

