#### Teaching methods used by nurses to deliver the intervention

##### Discharge Teaching Guide

The Discharge Teaching Guide was designed to guide nurses in how to conduct discharge teaching incorporating patient priorities identified using the ICAN, patient activation level identified using the PAM, and the six self-management domains identified in the PODS: reason for hospitalization, warning signs, medication plan, health behaviours, next appointments and which person to contact if needed. In the Discharge Teaching Guide, a first row for each domain of self-management reminds nurses to first check with the ICAN if patients experience any burden or priority that should be addressed for their return home. If this is the case, nurses must then report in the guide the proposed intervention to address this burden or priority. The Discharge Teaching Guide then supports nurses in addressing teaching objectives in each domain of self-management tailored to the patient's level of activation and suggests interventions to achieve these objectives. The guide also includes checkboxes to remind nurses to complete the PODS (see below) with patients to summarize the teaching content discussed for the management of their health at home. Teach-back is also recalled as a technique to be used to promote patient understanding and will have been taught to nurses during the intervention training.

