##### Patient-Oriented Discharge Summary

Patient-Oriented Discharge Summary (PODS) is a simple tool, containing meaningful information for patients presented in an easy-to-understand format [44]. This summary is a one-page document, with key information to be completed, such as the reason for hospitalization, warning signs to be monitored, who to call depending on the problem, the treatment plan and upcoming medical appointments. Participants will receive it at the beginning of the intervention, at the same time as the ICAN and the PAM. The PODS will be filled out during the hospital stay by the participant and the teaching nurse as teaching relevant to discharge occurs. Teaching nurses will review and verify on the day of discharge that the information written in the PODS correspond to the teaching content that was discussed (Fig. 2). Participants take the PODS home at discharge to serve as a reference for relevant and individualized discharge information in the post-discharge period.

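### Fidelity is read from the boxes ticked on the guide in use, so it cannot show whether the guide matched the patient's activation level and can overstate delivery of that part of the tailoring

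*Protocol article*

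**What the plan says.** In Study measures, Objective 1, fidelity of delivery "will be determined by entry of intervention activities on the Discharge Teaching Guide". The coverage intended is complete: "Nurses will use a Discharge Teaching Guide for each patient enrolled in the study". The nurse who delivers the teaching fills in the form, "on which they will record in check boxes each intervention they delivered to their patient", and the analysis is stated in one sentence: "A descriptive interpretation will be done to analyse the level of fidelity". The Data collection section describes the source as a "self-reported measure by teaching nurses of intervention fidelity during implementation phase".

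The rule for choosing the guide is in the Patient activation section: "The level of activation calculated with the PAM will define which category of Discharge Teaching Guide the nurses will use". Teaching objectives there differ between levels 1 and 2, level 3, and level 4. The level comes from 13 self-reported items, summed and then converted to a 0 to 100 score with a licensed scoresheet.

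The other strand of tailoring, the patient's own burdens and priorities from the ICAN, is written into the guide itself: "nurses must then report in the guide the proposed intervention to address this burden or priority".

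**The concern.** The intervention is tailored in two ways: to the patient's priorities and to the patient's activation level. The first leaves a trace on the fidelity form. The second is carried out by picking a guide, before any box is ticked. If the PAM is not completed, is scored wrongly, or the wrong category of guide is picked up, the form can still be filled in completely.

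This matters because the Discussion presents activation as the concept not yet applied to discharge preparation after acute hospitalization. The Data analysis section also plans to estimate an effect size for sizing later studies. If activation tailoring failed unnoticed, neither a positive nor a null preliminary result could be attributed to it, and the later hybrid trial would be designed on an untested belief that it had been delivered.

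**Working it through.** **Which component each measure can see.** All sources are in the Protocol article.

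| Element | Where it is fixed | Visible in the stated fidelity measure? |
|---|---|---|
| Teaching activities delivered | Study measures, Objective 1 | Yes, by nurse check box |
| ICAN priority and response to it | Discharge Teaching Guide section | Yes, written in the guide |
| Guide category agrees with PAM level | Patient activation section | No, not named |
| Share of enrolled patients with a completed guide | Study measures, Objective 1 (intention only) | No, no denominator stated |

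The other Objective 1 measures in the article do not fill the gap. AIM, IAM and FIM record nurses' perceptions. The post-implementation focus group concerns implementation strategies. The numerical feasibility thresholds in Data analysis cover recruitment (above 50%), loss to follow-up (below 20%) and outcome completion (above 80%).

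**Denominator.** The article states no fidelity figure to reproduce. The planned posttest sample does reproduce: 30 eligible per unit-month × 0.50 × 2 months = 30 per unit per phase; × 3 units = 90 posttest patients; × 2 phases = 180, as stated in Participants and recruitment.

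**How far the two readings could diverge.** Let t be the share of activities ticked on completed guides, m the share of enrolled patients with no guide, and w the share of completed guides at the wrong activation level. The documents give none of these, so all three are assumptions. Taking t as the same on matched and mismatched guides:

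- over completed guides, ignoring match: t
- over all enrolled, ignoring match: t(1 − m)
- over all enrolled, matched guide required: t(1 − m)(1 − w)

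With t = 85%:

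| m | w | Completed guides only | All enrolled, matched guide |
|---|---|---|---|
| 0% | 0% | 85% | 85.0% |
| 0% | 10% | 85% | 0.85 × 0.90 = 76.5% |
| 10% | 10% | 85% | 0.85 × 0.90 × 0.90 = 68.9% |
| 20% | 20% | 85% | 0.85 × 0.80 × 0.80 = 54.4% |
| 30% | 20% | 85% | 0.85 × 0.70 × 0.80 = 47.6% |

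The gap runs from 0 to 85 − 47.6 = 37.4 percentage points. With t = 90%, m = 20% and w = 10%, the comparison is 90% against 0.90 × 0.80 × 0.90 = 64.8%. Both columns are shares of activities, so like is compared with like. The first column does not change with m or w, which is the defect in numerical form.

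**The case against.** The strongest reply is that little information is lost. The guide exists in level-specific categories, so a completed one shows which category was used. The PAM is completed for the same patient, so the match could be tabulated from planned material within a descriptive analysis. The protocol fixes the guide by PAM level and intends one for every enrolled patient. Nurse-completed checklists are a disclosed and legitimate choice, and the full protocol, the analysis plan and the additional file with progression criteria are not shown.

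Most of this stands, and it limits the point. It does not remove it: a rule saying which guide to use is what a fidelity measure should verify, and the measure as stated does not use the data that would verify it.

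Several stronger readings are tempting and are not supported:

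- **Patients without a guide are dropped.** No exclusion rule is written. They generate no entries, and the text does not say how they would be counted.
- **A wrong-level guide earns full marks.** No scoring rule is stated, only a descriptive interpretation.
- **Few patients will meet a teaching nurse because only 12 to 15 of the units' 54 nurses (17 + 22 + 15) are trained.** This is a headcount ratio. The documents give no link from it to the share of patients without a guide.
- **The measure is biased upward.** Self-report may inflate, but a busy nurse may also leave delivered activities unticked. Overstatement is possible, not shown.
- **Tailoring as a whole goes unmeasured.** The ICAN strand is recorded in the guide.

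**Conclusion.** The point holds in a limited form. Fidelity as defined rests on the delivering nurse's ticks within the guide in hand. It cannot detect a guide of the wrong activation level and so can overstate delivery of activation-level tailoring. Nothing else in the article checks that step. Coverage is a secondary issue: a guide for every enrolled patient is an intention, and the stated measure does not report whether it was met.

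The size is unknown. The 0 to 37 point range above depends wholly on assumed rates and includes zero. The point should be acted on because the better measure uses material the study already produces and bears directly on its feasibility objective. It is not an error that invalidates the design.

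**What to change.** In the descriptive fidelity analysis, report for all enrolled posttest patients:

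1. the number and percent with a completed Discharge Teaching Guide;
2. the percent whose guide category matches the PAM level recalculated from the item responses, with patients who have no guide or no PAM shown as separate categories;
3. activities ticked, overall and among patients with a matched guide.

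The cost is small. Where PAM item responses are not already held electronically, entry is 13 items × 90 patients = 1,170 values, plus the guide category for each patient. Scoring uses the scoresheet the study will already hold under licence. The reported fidelity may look less favourable.

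An optional extra concerns the patient-held summary. The article says "Participants take the PODS home at discharge", so a copy taken at the discharge-day review already planned would give a second record of which domains were covered. The main fix does not depend on it.

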#### Objective 2: To conduct a preliminary test of the nursing discharge teaching intervention

##### Health confidence

The Health Confidence Score (HCS) is an easy-to-obtain proxy measure for the patient activation construct [56]. As this instrument has been very recently validated, there are currently no other validation studies or studies that have tested that it as an activation proxy. However, many authors in the field agree on this fact, knowing that confidence is one of the underlying concepts of patient activation [57, 58]. The HCS is a short measure (4 items) of patients’ confidence to manage their health and engage with healthcare providers [56]. Four dimensions are explored: knowledge, self-management, access to help and shared decision-making. Items have four response options (3=strongly agree, 2=agree, 1=neutral, 0=disagree). Scores are reported for each item and the higher the score, the higher the confidence. A summary score is calculated with a 13-point scale by adding the individual items scores, with a range from 0 (4×disagree) to the ceiling 12 (4×strongly agree). This instrument has good internal consistency (Cronbach’s alpha = 0.82) and construct validity [56]. The HCS will be translated in French according to Wild’s method [53].

##### Readiness for hospital discharge

The Readiness for Hospital Discharge Scale–Short Form (RHDS-SF) is an eight-item self-reported questionnaire [59]. Four dimensions measure personal status, knowledge to manage the post-hospital period, the ability to adapt to new health needs and the expected support [59]. Each item is scored on a Likert scale from 0 to 10, with the highest score indicating better perceived readiness. A mean score of less than 7 indicates low ready for hospital discharge [6, 60]. The short form of the RHDS explains 93% of the scale variance and reliability was 0.79 [59]. Results of predictive validity for older people showed that patients with higher scores were less likely to be readmitted (OR = 0.89, CI (95%) = 0.80-0.98, *P* = 0.03) [61]. The nine-item RHDS-SF for older people available in French will be used although the validation has not yet been carried out [61].

##### Rate of and time to readmission

Rate of and time to readmission will be measured by consulting administrative hospitalization data 7 days after patient discharge. Only readmission for the index hospitalization will be included.

##### Experience with discharge care

Patients’ experience with discharge care process will be assessed 7 to 10 days after discharge with the 11 items of the Discharge Care Experiences Survey (DICARES) [62]. This instrument investigates three domains: coping after discharge (4 items), adherence to treatment (3 items) and participation in discharge planning (4 items). The answer for each item ranges from 1 (“Not at all”) to 5 (“To a very large extent”), with higher scores indicating more positive experience. The psychometric evaluation of the DICARES in older patients showed an excellent test-retest reliability (ICC=0.76, CI 95; 0.70, 0.82), satisfactory construct validity (rho = 0.54, *p* <0.01) and an acceptable internal consistency (Cronbach’s alpha = 0.82) [62, 63].

##### Sociodemographic and medical characteristics

The following baseline participants sociodemographic and health data will be collected from health electronic records and reported in a REDCap™ electronic case report form (eCRF): age, sex, number of chronic conditions, years living with a chronic disease, length of stay and use of home health care services before and after index hospitalization. To determine the number of chronic conditions, a list of 75 chronic conditions most relevant in multimorbidity and developed by experts in Switzerland will be used to retrieve data on chronic conditions from discharge data from electronic records and coded as 1=the condition is present and 0= the condition is absent [64]. Total number of chronic conditions will be calculated for each patient. Number of previous hospitalizations in the same hospital within the last year will be retrieved from administrative hospitalization data and patients will be asked for information about prior hospitalization in a different hospital. As cohabitation and education are usually not specified in health electronic records, these questions will be asked directly to the participants.

### Data analysis

#### Objective 1: Test the feasibility of implementing the nursing discharge teaching intervention

Domains-level data of the Determinants of Implementation Behavior Questionnaire (DIBQ) will be analysed as categorical data. The proportion of nurses responding “agree” or “strongly agree”, indicating that the domain is a facilitating determinant of implementation behaviour, will be reported for items and domain. The same will be done for hindering domains indicated by “disagree” or “strongly disagree” responses.

CS-PAM responses will be reported in a scoring spreadsheet provided by Insignia Health® and will be sent to the license supplier who will calculate and send back the scoring. Assessment of differences in nurses’ beliefs and attitudes about patient activation between pre- and post-implementation phase will be undertaken through comparison tests (Student’s *t*-test).

Descriptive statistical analyses will be conducted to obtain means and standard deviations of Acceptability of Intervention Measure (AIM), Intervention Appropriateness Measure (IAM) and Feasibility of Intervention Measure (FIM). Higher scores will indicate greater acceptability, appropriateness and feasibility. The intervention will also be considered as feasible within clinical practice and for pragmatic clinical research if the recruitment rate is higher than 50%, the loss to follow up is less than 20% and more than 80% of outcome measure are completed. Progression criteria that will inform the decision to conduct a larger and definitive trial are detailed in Additional material 7 [65].

Content analysis of focus groups will also be carried out to provide information on behavioural determinants for the intervention, as well as acceptability, appropriateness and feasibility of the implementation strategies [66]. The focus groups will be transcribed in verbatim and read through several times first to get a sense of the whole. Transcripts will be coded deductively, using the 18 TDF domains as well as acceptability and feasibility of the implementation strategies as categories. The results will be discussed in the research group on the one hand linking them to the results of the DIBQ survey and to understand more fully behavioural determinants for implementation, and on the other hand to explore, based on the implementation outcomes, which implementation strategies could be used best in future trials.

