### Participants and recruitment

A sample of 12–15 nurses (4–5 per unit) will be recruited on a voluntary basis to take part in the study. Their participation will involve being trained in the intervention, delivering it during the implementation phase, participating in qualitative and quantitative evaluations in the pre- and post-implementation phase of their teaching behaviours and feasibility of the intervention. Inclusion criteria for nurse participants will be registered nurses, employed full time (80–100% work rate).

Inclusion criteria for participants will be 50 years old or more, having two or more chronic conditions, being hospitalized for more than 48 h, an expected discharge home defined at the beginning of the hospitalization and fluent speaking, reading and writing in French [34]. The inclusion criterion of 50 and over was chosen because from this age onwards the prevalence of multimorbidity is constantly increasing [35]. These criteria are deliberately broad in order to obtain a sufficient diversity of patients to reflect the variations encountered in patients in real-world practice. Patients will be excluded if they are cognitively unable to give their informed consent.

As this is a feasibility study, there is no sample size calculation [36]. A convenience sample of 180 hospitalized patients (90 pretest/90 posttest) was determined based on an estimate of the number of patients meeting the criteria for inclusion in the medical units of 30 patients per unit month. With an estimated recruitment rate of 50%, 30 pretest and 30 posttest patients per unit could be recruited over a 2-month period to achieve the 180-patient sample. Pretest participants will be recruited before nurses’ training about discharge teaching to prevent contamination. All eligible patients will be informed about the study and recruited four preselected days per week in two sites and 2 days per week in the third site due to resources’ constraints. Patients in the control and intervention groups will be recruited within 2 days after admission. Patients eligible to participate will be identified by the units’ nurses trained on participants’ inclusion and exclusion criteria. They will routinely screen newly admitted inpatients and inform the researcher of eligible patients. During recruitment days, all eligible patients will be informed about the study and asked for participation.

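### The DIBQ outcome is change in the same 12–15 nurses, but its planned analysis is agree/disagree proportions that cannot show within-nurse change; the CS-PAM t-test is not stated as paired

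*Protocol article*

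**What the plan says.** Under Participants and recruitment: "A sample of 12–15 nurses (4–5 per unit) will be recruited on a voluntary basis to take part in the study". Their role includes "participating in qualitative and quantitative evaluations in the pre- and post-implementation phase of their teaching behaviours and feasibility of the intervention". This is one group of nurses seen twice.

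Under Data collection, the nurses' online questionnaires are given "at pre- and post-implementation phases to assess changes in barriers to implementation and beliefs and attitudes regarding the importance of patient activation". Study measures, Objective 1, lists change in behavioural determinants and change in nurses' attitudes as the outcomes and gives the timing: "The DIBQ will be completed by teaching nurses at pre- and post-implementation phase", and "The CS-PAM will be completed by teaching nurses at pre- and post-implementation phases". DIBQ items are scored from 1 to 7 and cover 18 domains.

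Under Data analysis, Objective 1:

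- **DIBQ:** "Domains-level data of the Determinants of Implementation Behavior Questionnaire (DIBQ) will be analysed as categorical data". The proportion of nurses who agree or strongly agree, "indicating that the domain is a facilitating determinant of implementation behaviour, will be reported for items and domain"; the same is planned for disagreement as a sign of a hindering domain. No change measure is named.
- **CS-PAM:** differences in "beliefs and attitudes about patient activation between pre- and post-implementation phase will be undertaken through comparison tests", with Student's t-test in brackets. Paired or independent is not stated.

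Under Data analysis, Objective 2, almost the same phrase covers the comparison of pretest and posttest patients, who are different people.

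**The concern.** For the DIBQ, the declared outcome and the stated analysis do not match. The outcome is change in the same nurses; the analysis is a set of proportions on a collapsed scale. Set side by side, two proportions show the net shift but not who moved, and a nurse who moves between two scores in the same category does not count at all. With 12–15 nurses there is little information to spare.

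For the CS-PAM, the wording leaves the analyst to choose. Because the independent patient groups get nearly the same wording, an analyst could run the independent-samples form on the nurses too. That would ignore the pairing, widen the interval and hide real change. The article does not mention linking a nurse's two questionnaires. If they were collected without a link, a paired analysis could not be recovered later, so the point is best settled before collection.

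**Working it through.** **Inputs from the article.** Three units with 4–5 nurses each: 3 × 4 = 12 and 3 × 5 = 15, which reproduces the stated 12–15. No alpha, power, effect size or SD is given for the nurse outcomes, so there is no plan figure for power to reproduce.

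**Assumptions, not in the article.** Two-sided alpha 0.05, equal SDs before and after, a true shift of 0.8 SD, and pre–post correlation r from 0 to 0.7. The DIBQ counts below are illustrative.

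**1. DIBQ: what two proportions can and cannot show.** One nurse crossing the cut moves a proportion by 1/15 = 6.7 points or 1/12 = 8.3 points. Suppose 15 nurses, of whom 6 agree before and 11 after. The net gain is 5, but the same two proportions fit every row here:

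| Nurses moving up | Nurses moving down | Exact McNemar p |
|---|---|---|
| 5 | 0 | 0.062 |
| 6 | 1 | 0.125 |
| 7 | 2 | 0.180 |
| 8 | 3 | 0.227 |
| 9 | 4 | 0.267 |

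With 12 nurses and 5 rising to 9, the range is 4 up and 0 down (p = 0.125) to 7 up and 3 down (p = 0.344). The p-values only show how different the underlying patterns are; the planned output would be identical throughout.

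**2. CS-PAM: cost of an unpaired test on paired data.** In SD units the standard error of the change is √(2(1−r)/n) with n−1 degrees of freedom when paired. The unpaired test uses √(2/n) with 2n−2.

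Simulated power for a 0.8 SD shift (100,000 replicates, both tests applied to the same correlated data):

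| r | Unpaired, n=12 | Paired, n=12 | Unpaired, n=15 | Paired, n=15 |
|---|---|---|---|---|
| 0 | 46.9% | 43.5% | 56.2% | 53.2% |
| 0.3 | 46.5% | 57.2% | 57.4% | 68.4% |
| 0.5 | 46.2% | 71.5% | 58.7% | 82.2% |
| 0.7 | 46.1% | 90.3% | 60.8% | 96.2% |

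The exact noncentral-t values for the paired test at r = 0.5 are 71.4% and 82.1%, in agreement.

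**3. Interval width at r = 0.5.** The ratio of paired to unpaired width is √(1−r) × t(n−1)/t(2n−2).

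- n = 12: 0.707 × 2.201/2.074 = 0.750, so the paired interval is 25% narrower and the unpaired one 1/0.750 = 1.33 times as wide.
- n = 15: 0.707 × 2.145/2.048 = 0.741, so 26% narrower, or 1/0.741 = 1.35 times as wide.

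**4. Direction of the error.** With no true change, the unpaired test's actual type I error (nominal 0.05) is 0.020–0.022 at r = 0.3, 0.007–0.009 at r = 0.5 and 0.001–0.002 at r = 0.7. It rejects too seldom.

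**The case against.** A reader might infer that the plan never analyses within-nurse change in the CS-PAM, or that it prescribes an unpaired test. The article supports neither. It does plan a pre/post difference, Student's t-test includes the paired form, and wording shared with the patient comparison shows ambiguity, not the same test. The choice may also be settled in a fuller document. Taken alone, the CS-PAM point would be only a missing detail.

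A reader might also infer that no pre-to-post DIBQ comparison is intended. Since the questionnaire is given twice to assess change, the fair reading is that proportions from both phases will be set side by side. That objection stands. What remains is that such a comparison is net and categorical. The categories suit their purpose of labelling domains as facilitating or hindering, so they should stay. They do not deliver the declared change outcome, and here the article states the method and does not leave it open.

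It is also fair to say that the feasibility decision does not turn on these measures. The numerical thresholds concern recruitment above 50%, loss to follow-up below 20% and more than 80% of outcome measures completed. The further progression criteria are in an additional file that is not shown. Nothing says the questionnaires are unlinked, and the study makes no power claim. These points limit the impact but do not remove the mismatch.

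**Conclusion.** The point holds in limited form. For the DIBQ, the stated analysis cannot show the outcome that the article defines: within-nurse change is not recoverable from the planned proportions, and movement within a category is lost. For the CS-PAM, the test is ambiguous and should be named.

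If the CS-PAM test were run unpaired, power at r = 0.5 would be about 46–59% against 71–82%, with an interval about a third wider. This rests on the assumed 0.8 SD shift, alpha and correlation. The gain from pairing is smaller at r = 0.3, and at r = 0 there is none. With positive correlation the error is conservative, so it would not create false positives. It is not shown that most of the available information is discarded: pairing reduces the variance of the difference by a fraction r, which is half at r = 0.5.

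These are secondary measures in a feasibility study and do not enter the stated numerical thresholds. The impact is minor to moderate.

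**What to change.** - **Linkage:** state that each nurse's pre and post questionnaires carry the same study code, and that the code goes with the CS-PAM data sent to the licence holder so that scores come back linked.
- **DIBQ:** keep the agree/disagree proportions for both phases. Beside them, report the mean within-nurse change per domain on the 1–7 scale with a 95% CI, for nurses with both measurements. With 18 domains and 12–15 nurses, present this as descriptive, with no significance claim across domains.
- **CS-PAM:** name a paired t-test and report the mean within-nurse change with its 95% CI.

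The cost is a few sentences of analysis text and one identifier field on the online questionnaires. No additional nurses, visits or items are needed.
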